# Prefabricated foot orthoses compared to a placebo intervention for the treatment of chronic nonspecific low back pain: a study protocol for a randomised controlled trial

**DOI:** 10.1186/s13047-018-0299-5

**Published:** 2018-10-16

**Keywords:** Randomised controlled trial, Prefabricated foot orthoses, Chronic nonspecific low back pain, Gluteus medius, Transversus abdominis, Foot type

## Abstract

**Background:**

Prefabricated foot orthoses are used to treat chronic nonspecific low back pain, however their effectiveness and potential mechanism of action is unclear. The primary aims of the study are to investigate the effectiveness of prefabricated foot orthotic devices for reducing pain and improving function in people with chronic nonspecific low back pain over 52 weeks.

**Methods:**

This study is a participant and assessor blinded, parallel-group, superiority randomised (1:1) controlled trial. The study will recruit 60 participants aged 18 to 65 years with chronic nonspecific low back pain. Participants will undergo randomisation to a control group (The Back Book) or an intervention group (prefabricated foot orthoses and The Back Book). The primary outcome measures will be change in pain and function from baseline to 12 (primary time point), 26, and 52 weeks. Secondary outcome measures include: gluteus medius muscle activity and transversus abdominis muscle thickness from baseline to 12 weeks, physical activity over 12, 26, and 52 weeks, and correlation between foot type and change in measures of pain and function. Number of hours per day and week that the prefabricated orthoses are worn, as well as, adverse events will be self-reported by participants. Data will be analysed using the intention-to-treat principle.

**Discussion:**

This trial will primarily evaluate the effectiveness of prefabricated foot orthotic devices for reducing pain and improving function in people with chronic nonspecific low back pain over 52 weeks. It is expected that this study will provide clinicians and researchers with an understanding of the role that prefabricated foot orthoses may have in the treatment of chronic nonspecific low back pain and a potential mechanism of action, and whether foot type influences the outcome.

**Trial registration:**

ACTRN12618001298202.

**Electronic supplementary material:**

The online version of this article (10.1186/s13047-018-0299-5) contains supplementary material, which is available to authorized users.

## Background

Globally, low back pain (LBP) is the greatest cause of disability and is one of the major contributors to disease burden [1]. Direct costs of back pain have been estimated to be over AU$1 billion, most of which are associated with medical treatment [2]. Further to this, an additional AU$8.15 billion is lost through reduced earnings and decreased productivity both at work and home [2]. Recurrence rates of LBP are high, with up to 44% of LBP sufferers experiencing a return of symptoms within twelve months, and 85% having a recurrence over their life-time [3].

The aetiology of LBP is multifactorial with individual characteristics, psychosocial factors, and occupational demands linked to the development of the condition [3, 4]. Due to the varied nature of LBP, up to 85% of cases are classified as nonspecific [5], with the majority of these lasting for periods of greater than 3 months [6]. In such cases the LBP is referred to as chronic nonspecific LBP. Chronic nonspecific LBP is associated with high levels of pain, disability, depression, and reduced quality of life [7]. The evidence for the extensive range of chronic nonspecific LBP treatments has mixed levels of quality and shows highly variable outcomes [8–10].

Foot orthoses are one of the many treatment options available for chronic nonspecific LBP. The justification for the use of foot orthoses to treat chronic nonspecific LBP is based on several theoretical therapeutic mechanisms. These include reducing excessive or abnormal foot pronation [11, 12], achieving realignment of more proximal structures of the lumbopelvic-hip complex through adjustment of pronated foot posture [13, 14], and to increase the contact area of cavus feet so that shock absorption is improved [14, 15]. However, despite widespread use of this form of therapy, the evidence for the efficacy of this treatment for reducing pain and improving function in chronic nonspecific LBP suffers is limited.

A recent systematic review and meta-analysis reported that there are a lack of high quality trials investigating the use of foot orthoses to treat chronic nonspecific LBP [16]. Overall, the trials included in the systematic review were of moderate methodological quality, and had high heterogeneity, potentially masking the true extent of the beneficial effects of foot orthoses. Further to this, most of these trials used customised orthoses that were modified for individual participants [17–20], and limited their outcomes to changes in pain and function over twelve weeks or less. Providing individualised devices has the potential to reduce power and limit generalisability. Additionally, limiting follow-up to the short term may result in unobserved effects and the inability to determine if the effect remains over the longer term. Due to complex nature of chronic nonspecific LBP, measuring other domains that LBP affects, such as the level of physical activity [21], may help to better understand the response to orthotic devices.

Like the effectiveness of foot orthoses for chronic nonspecific LBP, the mechanism of action is similarly inconclusive. While previous research has demonstrated that foot orthoses can alter the kinematics of proximal structures [13], the effects have been found to be small, inconsistent and primarily seen in the foot and tibia rather than extending proximally [22]. So while it is possible that small changes may be significant for the development of pathology, due to the repetitive nature of gait, the lack of a homogenous kinematic effect indicates that alterations to kinematics may not be the primary action of foot orthoses in the treatment of more proximal injuries, such as chronic nonspecific LBP [13].

An alternative mechanism of action of foot orthoses is by influencing muscle activity, with some research demonstrating that this is the case when walking and running [23]. This includes changes to timing and intensity of contraction of muscles of the lower leg and thigh [24], and the superficial muscles of the lower back [25]. However, it is unclear how foot orthoses may have this effect and whether or not it is beneficial [23]. Nevertheless, the potential for proximal muscle activity to be altered with the use of foot orthoses may be significant in the treatment of chronic nonspecific LBP, as this condition is associated with dysfunction of deep trunk muscles such as the transversus abdominis [26], and weakness of hip muscles including gluteus medius [27].

Current evidence regarding the efficacy of foot orthoses for treatment of chronic nonspecific LBP, particularly in the long term, is inconclusive, as is the potential effect of foot orthoses on more proximal hip and trunk muscle function. This randomised controlled trial aims to investigate the effectiveness of prefabricated foot orthoses compared to a placebo intervention on pain and function in people with chronic nonspecific LBP after 12, 26, and 52 weeks. The secondary aims include determining the effect that these interventions have on participants’ gluteus medius muscle activity and transversus abdominis muscle thickness over 12 weeks, and physical activity over 12, 26 and 52 weeks. Additionally, the effectiveness of the interventions on pain and function per foot type (supinated, neutral, or pronated), as well as, intervention adherence and adverse events will also be investigated.

## Methods

### Design

This is a two-armed, parallel-group (intervention versus control), participant and assessor blinded superiority randomised (1:1) controlled trial (Fig. 1). Allocation concealment will be used to prevent selection bias by the use of sequentially numbered, opaque sealed envelopes containing a permuted block random allocation schedule with mixed block lengths of four and six participants. The trial will be conducted at the University of Newcastle Ourimbah Campus and the Podiatry Clinic at Wyong Hospital, both located in NSW, Australia. The trial has been prospectively registered on the Australian New Zealand Clinical Trials Registry (ACTRN12618001298202). The results of this trial will be reported using the CONSORT statement [28].

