### Interventions

Participants in the control group will receive ‘The Back Book’ educational booklet (Additional file 1) which contains written information about techniques for dealing with back pain. It has been demonstrated that this booklet has no significant effect on improving pain or function in people with chronic nonspecific LBP [31].

The intervention group will also receive ‘The Back Book’. In addition, they will be issued a pair of Formthotics™ prefabricated foot orthoses (Foot Science International Ltd., Christchurch, New Zealand, Fig. 2). The prefabricated foot orthoses will be heat moulded to fit the participant’s feet as per the manufacturer’s instructions. The devices will be worn in the participant’s usual footwear for 1 year from baseline. Wearing in instructions will be provided by the therapist (registered podiatrist), issuing the intervention. During the fitting process participants are shown, by the therapist, how the devices are fitted to their footwear. Participants are instructed to wear the devices as much as possible and that they may change them to other suitable shoes. Shoe suitability will be discussed as part of the fitting process. Participants in the prefabricated orthotic group will be provided with a usage diary. This and each intervention will be provided to participants by the therapist who is located in a separate room, after baseline questionnaires and clinical measurements are completed.

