Measurement of proximal muscle response to the intervention will help determine if foot orthoses induce changes in muscle function over 12 weeks. It is possible that this is a potential mechanism for any therapeutic effect of foot orthoses for chronic nonspecific LBP that may be demonstrated by this trial. Previous research on the potential mechanism of action of foot orthoses has tended to focus on kinematic and shock attenuation paradigms, with findings from meta-analyses indicating small and often clinically insignificant effects [59]. Fewer studies have focused on the neuromuscular paradigm, limiting pooled analyses. However, of the trials that have investigated the neuromuscular response to foot orthoses, the focus has largely been on the muscles in the lower leg [59]. Of these trials, the effect of a range of different foot orthotic designs has been evaluated, with the consistent outcome being increases in muscle amplitude in response to the orthotic [23, 59]. Similar increases in gluteus medius and transversus abdominis muscle activity have been found in response to foot orthoses however these trials have included fewer than twenty participants, investigated the immediate effect of the devices, and included people without chronic nonspecific LBP [25, 60, 61]. We plan to build upon previous research by evaluating the effect that prefabricated foot orthoses have on gluteus medius activity and transversus abdominis muscle thickness in sixty people with chronic nonspecific LBP over 12 weeks.

Previous research investigating foot orthotic devices for a range of other musculoskeletal conditions have used flat insoles in the control group [57, 62, 63]. However, flat insoles may have some therapeutic or biomechanical effect and are therefore more appropriately referred to as a sham intervention [64]. Additionally, some participants with chronic nonspecific LBP may benefit from the potential cushioning of a flat insert (for example those with a pes cavus foot type). Therefore the authors believe that an education-based intervention, ‘The Back Book’, is better suited to act as a placebo intervention because it has been shown to be ineffective for reducing pain and function in people with chronic nonspecific LBP [31].

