It is also anticipated that this trial will help develop an understanding of the proportions of foot types in people with chronic nonspecific LBP, so that future studies can be adequately powered for the interaction between foot type and foot orthoses. Previous research has either not defined participant’s foot type [16], or has focused only on pronated feet [19]. Castro-Mendez and colleagues [19] found a significant effect in favour of foot orthoses for reducing pain in those with chronic nonspecific LBP and pronated feet, however the effect in relation to other foot types is unknown.

This protocol is based on the SPIRIT guidelines [65]. However, given that this trial will use a placebo intervention for the control group, sources of bias associated with this type of design are important to consider. We will attempt to control ascertainment or detection bias [66], by having two levels of participant information statements and consent forms and maintaining allocation concealment. Nevertheless, some participants such as those that know each other, may discuss their interventions outside of the trial and therefore discover the differences. Given that this trial is designed to have a placebo intervention, a ‘no-treatment’ group was not used because of the potential for participants’ results or behaviour to be influenced by resentful demoralisation [66]; however, this may still occur if participants become aware of the different interventions.

Therefore, whilst we have designed the trial to maintain methodological rigour and control for potential sources of bias associated with a placebo control group, there are still some potential limitations. We will not be able to account for a potential placebo effect or prevent participants from undergoing other treatments external to the study, both of which may confound any treatment effects. We will record any external treatment participants undertake to help with the interpretation of the results.

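### The trial is labelled participant-blinded and placebo-controlled, but it compares orthoses plus booklet with booklet alone, on self-rated primary outcomes, among participants who know what they received

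*Protocol article*

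**What the plan says.** All references are to the protocol article.

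- **Labels.** Methods, Design, states: "This is a two-armed, parallel-group (intervention versus control), participant and assessor blinded superiority randomised (1:1) controlled trial". The aim at the end of the Background is to "investigate the effectiveness of prefabricated foot orthoses compared to a placebo intervention on pain and function", and the title also names a placebo comparator.
- **What each arm receives (Interventions).** Controls get The Back Book, an "educational booklet (Additional file 1) which contains written information about techniques for dealing with back pain". The other arm gets the same booklet. "In addition, they will be issued a pair of Formthotics™ prefabricated foot orthoses", which a registered podiatrist moulds and fits, with wearing-in instructions and advice on shoes. "Participants in the prefabricated orthotic group will be provided with a usage diary"; controls have none.
- **What participants are told (Participants).** Everyone first reads a general statement that there are two groups and that the treatment will be a conservative one in common professional use. After randomisation a second statement describes the treatment they were assigned.
- **Who rates the outcomes (Data collection sessions; Primary outcome measurements).** The pain scale and the Oswestry index are completed by participants, and are mailed at 26 and 52 weeks.
- **Rationale and limitation (Discussion).** The booklet "is better suited to act as a placebo intervention because it has been shown to be ineffective for reducing pain and function". Further on: "We will not be able to account for a potential placebo effect".

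**The concern.** A placebo control is meant to make the arms alike in expectation, contact and ritual, so that what remains can be credited to the active ingredient. A comparator that is merely inert does not do this. Here nothing in the control arm resembles the device, and the people who know which treatment they received also supply both primary outcomes.

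What is at stake is the claim, not the validity of the randomisation. If the labels stand, a positive result at 12 weeks will be read as orthoses beating placebo. The same result could come partly or wholly from expectation, extra podiatrist contact or daily self-monitoring.

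**Working it through.** **1. Remove what the arms share.**

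| Component | Orthosis arm | Control arm |
|---|---|---|
| The Back Book | yes | yes |
| Moulded device | yes | no |
| Podiatrist fitting, wearing-in and shoe advice | yes | no |
| Wear diary over 12 weeks | yes | no |

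The booklet cancels. The randomised contrast is the device, the contact and the diary together, on top of the booklet.

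**2. Ask who is masked to what.** The second information statement tells participants their own treatment. What is withheld is the content of the other arm. That is masking to the alternative, not to treatment received.

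**3. Match masking to outcome.**

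| Outcome | Rater | Does assessor blinding protect it? |
|---|---|---|
| Pain scale, Oswestry index (primary) | participant | no |
| Physical activity questionnaire | participant | no |
| Gluteus medius EMG, transversus abdominis ultrasound (secondary) | blinded assessor | it matters here |

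**4. Set the rationale beside the concession.** The Discussion chooses the booklet as placebo because it does not work. It then says that a placebo effect cannot be accounted for. A control that leaves the placebo effect unaccounted for is not doing the job the label gives it.

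**5. Check the bias terms.** The Design section correctly ties allocation concealment to selection bias. The Discussion lists it, with the two-level information statements and consent forms, as a means of controlling ascertainment or detection bias. Concealment ends at assignment and cannot affect how outcomes are later reported.

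**6. Illustrate the size.** Inputs from the Sample size section: difference 2, SD 2.5, power 80%, type I error 5% (taken as two-sided), non-adherence 20%, 30 per group.

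The plan's figure reproduces: n = 2 × (1.960 + 0.842)² × 2.5² / 2² = 24.5, rounded up to 25 per arm; 25 × 1.2 = 30.

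Let b be a purely contextual difference in pain score, with no effect of the device itself. The protocol gives no value for b, so 0.5 and 1.0 points are assumptions. SE = 2.5 × √(2/n): 0.645 at n = 30, and 0.722 at n = 24 (30 × 0.8). The chance of p < 0.05 comes from the noncentral t distribution with noncentrality b/SE and 2n − 2 degrees of freedom.

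| b (assumed) | b/SE, n = 30 | Chance | b/SE, n = 24 | Chance |
|---|---|---|---|---|
| 0 | 0 | 5% | 0 | 5% |
| 0.5 | 0.775 | 12% | 0.693 | 10% |
| 1.0 | 1.549 | 33% | 1.386 | 27% |

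This is an unadjusted comparison. The planned ANCOVA would change the SE by an amount that depends on the baseline correlation, which is not given. A larger sample would not remove b.

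**The case against.** The authors can fairly say four things.

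- **It is disclosed.** The Abstract states the contents of both arms exactly, and the Discussion admits that participants may discover the difference and that a placebo effect is not handled. This stands, and nothing is hidden. But the title, aim and design keep labels that the Discussion undercuts.
- **The control was a reasoned choice.** Flat insoles were rejected because they may have an effect of their own, and a no-treatment arm because of resentful demoralisation. This also stands. An add-on comparison is legitimate, and the point does not call for a sham insole.
- **Expectation was partly addressed.** The neutral general statement presents either treatment as one in normal use, and the two-level consent withholds the alternative. These are real safeguards and may limit disappointment among controls. They do not equalise contact, monitoring or the experience of receiving a fitted device.
- **The percentages rest on an assumption.** They do, and they describe no property of the randomised test.

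Three stronger readings are tempting and unsupported. A reader might infer that the trial's type I error is 12% to 33%. It is not: if the package shifts pain through expectation, rejecting equality of package and booklet is correct, and only crediting the device would be wrong. A reader might infer that no outcome is protected, but the EMG and ultrasound measures are taken by a blinded assessor. A reader might also think a matching diary for controls would solve the problem. It would balance neither device nor contact, and an activity diary could itself alter the physical activity outcome.

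**Conclusion.** The point holds as a conflict between the labels and the design. Participants are unaware of the alternative arm, not blinded to treatment. The comparator is an add-on control, not a placebo. The primary outcomes have no protection from assessor blinding. The randomised estimate remains valid for the effect of adding the whole orthosis package, including expectation, contact and self-monitoring, to The Back Book. It cannot be attributed to the orthosis alone.

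The documents do not allow the contextual share to be sized. The range of about 12% to 33% at 30 per arm depends on an assumed contextual difference of 0.5 to 1.0 points, no device effect and SD 2.5. It illustrates the risk of misattribution only. The conclusion about the labels depends on none of these numbers.

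**What to change.** 1. In the title, aim, design and planned conclusion, describe the comparison as *prefabricated orthoses plus The Back Book versus The Back Book alone*.
2. Replace the participant-blinding claim with *participants unaware of the alternative intervention*. Keep the assessor-blinding claim, and say that it bears on the EMG and ultrasound outcomes.
3. State that the primary estimate is the effect of adding the whole package, including expectation, contact and self-monitoring, and that it will not be reported as superiority to placebo.
4. In the Discussion, credit allocation concealment with preventing selection bias only.
5. Optional: one brief expectation item in both arms after allocation, reported by arm. Any question on whether participants learned of the other treatment should wait until the 52-week outcomes are in, because asking at 12 weeks could prompt unmasking before the 26- and 52-week questionnaires.

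Items 1 to 4 cost wording only and leave sample size, randomisation and interventions unchanged. Item 5 costs at most two short questions. The real price is a less ambitious claim.

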**Fig. 1 Fig1:**
[figure not shown]
Flow of participants through the trial

### Ethical approval

Ethical approval has been provided by the University of Newcastle Human Ethics Committee (H-2017-0345). Written informed consent will be obtained from participants before baseline testing.

### Participants

Participants will be aged 18 to 65 years, male, female or of indeterminate sex, proficient in English, have a history of chronic nonspecific LBP as confirmed by a general practitioner (GP), and report a score of 3 or greater for their chronic nonspecific LBP on the numeric pain rating scale to ensure a minimally clinically important change for this score can be measured [29]. The chronic nonspecific LBP will need to be located between the ribs and buttock creases to be eligible [30]. Participants will be excluded if they have significant or worsening signs of neurological deficit, inflammatory joint disease, are pregnant, or have previous (within the last 12 months) or current use of foot orthotic devices.

Potential participants will be recruited using an advertising flyer or by a participating GPs informing their patient of the project. Participants must be seen by a GP prior to commencing of the study so that chronic nonspecific LBP can be diagnosed and their eligibility for the study verified.

GPs in the Central Coast region of NSW will be contacted via phone or in person by one of the researchers prior to participant recruitment. They will be invited to participate in the project as a referring health professional. If they agree to participate, they will be asked to assess and diagnose patients presenting with chronic nonspecific LBP and then screen the patient as per the study’s inclusion and exclusion criteria. Additionally, the advertising flyer will be displayed at health professional clinics in the Central Coast region of NSW and will have the researcher’s contact details on it. Potential participants that see the flyer and firstly contact the researcher will be referred to the University of Newcastle Ourimbah Campus GP to have their LBP assessed and then screened against the study’s inclusion and exclusion criteria for chronic nonspecific LBP. The GP screening participants will provide eligible participants with a general participant information statement. This contains one the researcher’s contact details so that interested participants can contact the researcher to organise baseline testing. The general participant information statement will inform potential participants about the study’s requirements, including that participants will be randomised to one of two groups and receive a conservative (non-surgical and not pharmacological) intervention commonly used by health professionals. It will also advise participants that once they are randomised to a group, they will be given another participant information statement that will provide specific information about their assigned intervention.

